### Sample size

A total of 100 patients would be recruited for the study. A meta-analysis has found an effect size of 0.88 for clozapine with ECT as compared to clozapine alone (
Wang *et al.*, 2018). The sample size for this study was calculated using a more conservative estimate of effect size 0.6 for a sham-controlled trial, to account for potential placebo response in the sham group. Given an effect size of 0.6 between the treatment groups for change in positive symptom severity, a minimum sample of 45 in each group would have 80% power to detect post-treatment differences between the two groups with an alpha of 0.05 in a two independent sample t-test. In order to account for dropouts, we propose to recruit 50 patients in each group. For comparison studies between patients and healthy controls, a sample size of at least 100 healthy subjects would offer optimal power as per the sample size of previous neurobiological studies in this area (
Goyal *et al.*, 2011;
Mouchlianitis *et al.*, 2016;
Raymond *et al.*, 2022).

### Allocation

**
*Sequence generation.*
** Consenting patients would be randomly assigned using computer-generated codes to true/sham ECT. Random allocation of two treatments (ECT and SHAM) for three study centers with unequal strata sizes of 60, 20 and 20 would be carried out in Stata ver.15.1 (
*StataCorp.,* 2017). This procedure would provide a sequence of treatments (ECT & SHAM), which would be randomly permuted in blocks of varying sizes and order. An independent statistician would manage the randomisation and allocation concealment. The allocation sequence generation will be centrally coordinated at NIMHANS.

**
*Concealment mechanism.*
** Allocation concealment would be ensured through sequentially numbered sealed opaque envelopes. The person administering ECT would allocate the study arm by opening the sealed envelope on the first day of intervention after anaesthesia and muscle relaxant are administered.

**
*Masking.*
** The participants, their care-givers, investigators, safety assessors, outcome assessors, treating psychiatrists, data managers and data analysts would be blinded to the allocated study arm. Staff involved in the ECT administration including an independent psychiatrist (not involved in regular clinical care of the patient), anaesthesiologist, and paramedical staff would become unblinded thereafter. Paramedical staff in the recovery room would remain blinded to the study arm and would assess the time to reorientation and post ECT adverse effects. Independent assessors would monitor study outcome and they would remain blinded about the study arm till the end of post-RCT assessments. As the risk of unblinding would be high on immediate post-ECT adverse effect evaluation, outcome assessors would remain blinded to the immediate adverse effects. The treating clinical team would also remain blinded to study arm and immediate cognitive/behavioral adverse events till the end of post-RCT assessment. To maintain the rigorous blinding, two independent assessors would rate the safety and outcome measures.

ECT related records will be maintained by the ECT administrators who are unblinded to the study. ECT procedure details including the details of seizures will be maintained in the ECT suite securely by the ECT administrators. The device used in this study shows an online digital display and provides a digital copy of the EEG which will again be securely stored by ECT administrator. Adverse outcome assessors maintain the adverse effect assessment records securely under the supervision of the psychiatrist administering ECT. This psychiatrist will decide on intimating the adverse events to the clinical teams without compromising the clinical needs of the patients and maintaining the blinding as much possible.

**
*Emergency unblinding.*
** Serious adverse events (SAE) would be reported to the trial management group (TMG) and data and safety monitoring board (DSMB), which would assess for suspected unexpected serious adverse reaction (SUSAR); the patient, caregiver, clinical team and the investigators may be unblinded at their discretion. Otherwise, all participants would be unblinded at the termination of the trial (either after completion of nine sessions or premature termination for any other reason). Assessment of blinding efficacy would be done on patients, adverse event assessors and outcome assessors after the last (scheduled/terminated) blinded intervention session using a 5-point likert scale (
Bang *et al.*, 2004).

**
*Trial procedures and evaluations.*
** In addition to the above discussed screening tools and outcome tools, all participants would be assessed using a comprehensive semi-structured proforma to collect the socio-demographic and clinical details would be collected (
[name] *et al.*, 2022). Clinical ratings would be performed by mental health professionals. They would be trained in administering the clinical rating scales and inter-rater reliability assessments would be performed for the primary outcome measure. Comprehensive data collection forms would be available with the investigators and would be made available on reasonable request.

Multi-modal neurophysiological data (magnetic resonance imaging [MRI], EEG, cortical perturbation using TMS-tDCS, HRV) would be acquired before and after interventions to identify predictive factors and understand mechanistic basis of the ECT outcome. Clinical and neurobiological evaluations would be repeated even after the end of the open label phase. Also, neuroplasticity gene polymorphisms (brain derived neurotrophic factor [BDNF] and catechol-O-methyltransferase [COMT] genes) will be assessed alongside clinical and neurophysiological data to identify the predictors of clinical response. At least 100 subjects matched (as a group) for age, sex, education, handedness, and socio-economic status would be chosen for the comparative analyses of neurobiological studies. They would undergo a one-time baseline assessment of clinical and neurobiological parameters.
Figure 2 depicts the assessment timepoints.

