### Intervention

**True ECT**: Thrice-weekly, bifrontal ECT would be provided for a minimum of nine sessions and would be extended till a plateau is achieved in clinical response. ECT would be provided with a NIVIQURE ECT device (current: 800mA, pulse frequency: 75 pulses per second, pulse-width: 1ms). Modification would be provided with short general anaesthesia and muscle relaxants (usually with thiopentone 2–4 mg/kg & succinylcholine 0.5 mg/kg). Alternative modification agents would be considered if there are any medical indications. The electrodes would be placed 5 cm above the outer canthus of each eye, along a vertical line perpendicular to an imaginary line connecting the two pupils. ECT would be administered as per the standard procedure by a team of psychiatrist(s), anaesthesiologist, nursing and other paramedical professionals.

The seizure threshold would be determined during the first ECT session through titration method. The stimulation would be initiated at 30mC with increments of 30mC until adequate seizure is achieved. The ECT administrator would initiate the stimulation at a higher dose depending on age and co-administration of anticonvulsants. From the subsequent sessions, patients would receive 1.5 times suprathreshold ECT. EEG would be recorded during the ECT with the NIVIQURE ECT–EEG device from left and right frontal pole leads (Fp1 and Fp2), referenced to bilateral mastoid processes. As per current guidelines, seizures would be considered adequate if there is evidence for generalized seizures observed in either the motor system (in the isolated limb) or in the typical morphology of EEG (
Ferrier & Waite, 2019). ECTs may be continued after nine sessions, if there are persisting symptoms and continuous improvement is observed.

After the 9th ECT session, ECT course would be terminated on achieving plateau in clinical response, i.e., if there is no change in the clinical status from the previous session in three consecutive sessions as measured by Sheehan-Clinician Global Improvement Global-21 scale (S-CGI-21) (

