### Participant timeline (
Figure 1)

**
*Patients*
**

**Step-1:** Patients prescribed ECT by the treating psychiatrist fulfilling eligibility criteria will be approached for participation in the trial. Consenting participants would be randomized to true/sham ECT administered thrice-weekly for nine or more sessions till achievement of plateau in clinical improvement. Pharmacotherapy will remain stable during the ECT course.

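### Participants are to be unblinded at nine sessions, although the randomised course may run past nine

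*Protocol article*

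**What the plan says.** The unblinding rule is in the Allocation section, under Emergency unblinding. Apart from unblinding after serious adverse events, "all participants would be unblinded at the termination of the trial (either after completion of nine sessions or premature termination for any other reason". The parenthesis has two branches, nine sessions done or an early stop, and none for a patient who goes on beyond nine.

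The course length is set elsewhere. On true ECT, Intervention states: "Thrice-weekly, bifrontal ECT would be provided for a minimum of nine sessions and would be extended till a plateau is achieved in clinical response". The same section adds: "ECTs may be continued after nine sessions, if there are persisting symptoms and continuous improvement is observed". After session nine, plateau is reached "if there is no change in the clinical status from the previous session in three consecutive sessions", judged on the S-CGI-21. Participant timeline, Step-1, covers both arms: patients are "randomized to true/sham ECT administered thrice-weekly for nine or more sessions till achievement of plateau in clinical improvement". The Figure 1 legend gives the randomised step as four to six weeks of true or sham ECT.

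Two other statements bear on blinding. The sentence after the unblinding rule places the check of blinding "after the last (scheduled/terminated) blinded intervention session". Masking says of the outcome assessors that "they would remain blinded about the study arm till the end of post-RCT assessments", and continues: "The treating clinical team would also remain blinded to study arm", also until the post-RCT assessment is over.

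**The concern.** The rule that ends participant blinding and the rule that ends the randomised course use different stopping points. A site that follows the first as printed tells an extended patient the arm while Step 1 is still running. In the sham arm, that patient would know there is no stimulus yet still be due further anaesthesia, because Intervention offers open-label ECT only once the blinded trial has ended (or the patient withdraws).

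Several measurements are still to come at that point: the S-CGI-21 ratings after each session, which decide plateau and so course length; the weekly SAPS, SANS, BPRS and AHRS ratings; and the post-RCT assessments. These feed the comparison of time to response and the mixed model at the end of the interventions (Data analysis). A patient who knows the arm may answer interview items differently or let the arm slip to the rater. Blinding of the patient is a main reason for having a sham arm here: the Background faults earlier trials for lacking one.

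**Working it through.** No figure in the protocol covers this point, so the check sets the rules side by side and converts weeks to sessions.

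**1. Does the extension apply to both arms?** The extension and plateau rules in Intervention stand under True ECT. Participant timeline, Step-1, gives nine or more sessions to plateau for true and sham alike, and the Figure 1 legend gives both arms the same duration. So sessions after the ninth belong to the randomised step in either arm.

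**2. When does the printed rule unblind?** Nine sessions at three per week take 9 / 3 = 3 weeks; at the reduced frequency of two per week, 9 / 2 = 4.5 weeks.

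**3. How much of Step 1 could follow?** The only stated duration is the 4 to 6 weeks in the Figure 1 legend. The legend gives no session frequency, so both are shown.

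- Thrice weekly: 4 × 3 = 12 to 6 × 3 = 18 sessions. Past the ninth: 12 − 9 = 3 to 18 − 9 = 9 sessions. Weekly ratings past that point: 4 − 3 = 1 to 6 − 3 = 3.
- Twice weekly: 4 × 2 = 8 to 6 × 2 = 12 sessions. Past the ninth: 0 (8 is below nine) to 12 − 9 = 3 sessions.

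**4. Does the plateau rule agree?** By that rule alone, a patient still improving at session nine needs three unchanged sessions after it and stops no earlier than session 9 + 3 = 12, unless another stopping reason applies. A patient unchanged over sessions 7 to 9 can stop at nine. Extension is thus an ordinary route for improvers.

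**5. What about a patient who stops at exactly nine?** The rule lets unblinding follow the ninth session. It does not place it after the post-RCT assessments, or after the clinical rating made 24 hours after the session (Outcomes). The first gap exposes post-RCT measures even without extension. The second reaches the primary outcome only if a site unblinds within those 24 hours.

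**6. Which outcomes are exposed?** The primary analysis uses the SAPS change to session nine (Outcomes; Data analysis), so ratings after session nine do not enter it. Interview-based secondary ratings are the most open to influence. Post-RCT measures such as MRI, EEG and heart rate variability do not depend on interview answers and are less open to this route.

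**The case against.** The strongest reply is that the parenthesis is loose wording. The operative event is the end of the trial, nine is the nominal length, and the contrast intended is between scheduled and premature ending. The sentence that follows supports this by tying the blinding check to the last blinded session. It is also true that no statement says outright that sessions after the ninth are blinded. This is probably what was meant, but it does not remove the need for a change, because the printed rule says something else. The other way out, that the blinded phase ends at nine, conflicts with Participant timeline and the Figure 1 legend.

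It is also fair that the size is uncertain. The range of 3 to 9 sessions needs uninterrupted thrice-weekly treatment, zero is possible at twice weekly, and no figure for extended patients exists. That stands.

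A reader might go on to infer that the Discussion understates the sham course, for example that 12 sham sessions followed by 9 open-label ones would make 21. The documents do not support this. The Discussion is speaking of sham patients who do not improve, and Intervention allows continuation past nine only with continuous improvement, so nine sham sessions is the expected course for them. All that remains is that the Discussion caps the open-label course at nine while Participant timeline, Step-2, gives it a duration like that of Step 1. That is descriptive prose which governs no procedure.

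**Conclusion.** The inconsistency is real and minor. As printed, a patient extended past nine sessions is unblinded during the randomised step, and a patient who stops at nine may be unblinded before the post-RCT assessments. The exposure is 3 to 9 sessions and 1 to 3 weekly ratings per extended patient if the legend's weeks are thrice weekly, or 0 to 3 sessions at twice weekly, in an unknown share of patients. It falls on secondary outcomes, mainly interview-based ones.

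Two stronger readings should be resisted. A reader might infer that the outcome raters lose their blinding; Masking keeps them and the treating team blinded to the end of the post-RCT assessments, so the risk runs only through the patient. A reader might also infer that the primary result is compromised; it is fixed at session nine, and the extension conflict does not reach it. This last conclusion assumes that the 24-hour rating is made before the participant is told the arm, an order that the rule leaves open.

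**What to change.** Change the parenthesis under Emergency unblinding so that each participant is unblinded only after the last Step-1 session, whether scheduled or premature, and after the post-RCT assessments are complete. This agrees with the timing of the blinding check and with the Masking rule for assessors, and it puts the 24-hour session-nine rating safely before unblinding.

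If the sponsor instead intends the blinded phase to end at nine, Intervention, Participant timeline and the Figure 1 legend would all have to say so, and blinded data after session nine would be given up. The first option is better.

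The cost is a short text amendment, with the notifications already set out under Protocol modification. The small downside is that extended participants stay blinded longer. At the same time the open-label length in the Discussion can be matched to Step-2 of Participant timeline, purely as a tidy-up.

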**Figure 2. f2:**
[figure not shown]
Gantt chart of the assessment timeline in patients. Grey boxes are scheduled timepoints of respective assessments. ECT
_n_= n
^th^ ECT session. *Weekly assessments during the course of treatment will be done every week even if frequency of ECT is reduced to 2/week.

### Neurobiological investigations

**MRI studies:** MRI data will be acquired with a 3T scanner (Ingenia CX, Philips). Structural MRI, resting-state functional MRI and Diffusion Tensor Imaging will be acquired as per the established protocol (
Parekh *et al.*, 2021). Magnetic resonance spectroscopy studies will be done to measure glutamate levels in the left dorsolateral prefrontal cortex and left temporoparietal junction based on their pathophysiological role in schizophrenia (
Fan *et al.*, 2017;
Younis *et al.*, 2020).

**Cortical reactivity and plasticity:** Motor cortical reactivity will be determined by employing single and paired-pulse TMS-EMG investigational approaches to determine the motor threshold, silent period, and intracortical inhibition/facilitation. We will also employ perturbation-based motor cortical plasticity experiments to quantify the magnitude and direction of change in motor evoked potentials with a single session of iTBS/cTBS/c-tDCS. The type of perturbation protocols used will mimic those used in the actual treatment protocols (
Mehta *et al.*, 2019).

**EEG:** Continuous resting-state EEG will be acquired for 20 minutes. Sixteen minutes of eyes-closed resting-state EEG would be acquired in two separate time blocks of 12 minutes and 4 minutes with an intervening 4-minute duration of an eyes-open EEG. EEG data will be acquired by a 64-channel amplifier with the electrode montage placed based on the international 10/10 system. All data will be referenced against an electrode centred on the midline between Fz and Cz, and sampled at 5 kHz (
Babiloni *et al.*, 2020;
Trujillo *et al.*, 2017)

**HRV:** 15-min resting ECG will be obtained to determine the beat-to-beat variability of heart rate, and the multitude of both time (SDNN, RMSSD, PNN50, triangular index) and frequency domain (low and high frequency) measures of HRV (
Task Force of the European Society of Cardiology and the North American Society of Pacing and Electrophysiology, 1996).

**
*Blood assay.*
** Blood samples will be collected from the ante-cubital vein into K
_2_ EDTA vacutainer tubes (Becton & Dickinson, U.S.A). DNA extraction will be carried out using the commercial spin column method (Qiagen, Inc.). Extracted DNA will be checked for quality assurance and stored at -80°C for later use. PCR amplification for SNP assays of selected functional polymorphic variants of COMT (
Chhabra *et al.*, 2018) and BDNF (
Strube *et al.*, 2014) genes will be performed. 

The details of the neurobiological data acquisition protocol will be described in a separate paper. 

### Data management

The multi-level data acquired from the enrolled participants would be quality checked and anonymised so that subject identifiers are removed. These data would be stored with a coded identification. Different streams of data (ex. Clinical, MRI, EEG etc.,) would be linked using codes to facilitate seamless retrieval of different data types.

### Data analysis

Anonymized coded data would be used for analysis. The primary outcome would be assessed as the change in SAPS scores from baseline to post-9th session of treatment using a two-sample t-test. The last observation carried forward method would be used to handle the missing data of those participants who had premature termination of the intervention. The percentage of responders between the two groups would be compared using logistic regression with estimates of adjusted odds-ratio (adjusting for variables including age, sex, duration of illness, antipsychotic daily dose, and anticonvulsant medications). Further, comparison of change in the symptoms scores between the two groups at the end of the interventions would be performed through linear mixed-effects model analysis. The time to response would be compared between the two groups using survival curves. Suitable imputation methods would be used for any missing data at specified time-points. Secondary outcome measures including other psychopathology rating scales, adverse effects and dropout rates would also be compared between the two groups.

The pre-processing of neurobiological data (where applicable – MRI/EEG data) will be done according to the internationally accepted processing pipelines. Data analysis will be carried out in two phases – a) association and b) prediction. The first phase will involve exploratory analyses with biographic (age, sex, etc.) and disorder-specific (including age-at-onset, medication, the severity of symptoms) features that influence MRI, EEG, TMS-derived neuroplasticity metrics, HRV, and gene polymorphism measures. These include traditional biostatistical procedures such as descriptive statistics and hypothesis testing for associations in order to identify any potential biomarkers of clinical response. The second phase of analysis will involve building predictive models that will be validated with an independent dataset. Here, instead of examining which individual measurements correlate with outcome measures, we seek to identify combination features (from resting-state fMRI as the primary objective; combining across data modalities will be the secondary objective) that can give the best prediction for the clinical outcome of proposed brain stimulation methods. State-of-the-art feature engineering/machine learning methods, such as gradient boosting/deep neural nets, will be used to train the model on a part of the acquired dataset. Lastly, causal models like Bayesian networks or mediational analyses will be explored to uncover potential causal relationships between study variables.

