## Methods

### Trial design

We employ a parallel-arm double-blind randomized sham-controlled design with an allocation ratio of 1:1 to determine the differential efficacy of add-on electroconvulsive therapy to sham-electroconvulsive therapy in clozapine-resistant/intolerant schizophrenia.

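### The primary t-test on SAPS change adjusts for neither baseline SAPS nor the stratifying centre: it is valid and meets its stated power, but gives up precision the trial could have at no extra patients

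*Protocol article*

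**What the plan says.** The protocol article states the primary analysis in one sentence under Data analysis: "The primary outcome would be assessed as the change in SAPS scores from baseline to post-9th session of treatment using a two-sample t-test". It names no covariate for this test. Baseline SAPS enters only by being subtracted.

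The Sample size section uses the same test, at a significance level of 0.05 and an assumed standardised effect of 0.6 on the change score. Its power statement is that "a minimum sample of 45 in each group would have 80% power to detect post-treatment differences between the two groups". The dropout allowance is stated separately: "In order to account for dropouts, we propose to recruit 50 patients in each group".

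Under Allocation, centre is a stratification factor: "Random allocation of two treatments (ECT and SHAM) for three study centers with unequal strata sizes of 60, 20 and 20", with permuted blocks of varying size. Trial design gives the ratio: "with an allocation ratio of 1:1".

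The Outcomes section has SAPS rated at baseline and weekly, so the baseline value should be on file for every randomised patient.

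Two further analyses appear under Data analysis. One is a logistic regression of response, "adjusting for variables including age, sex, duration of illness, antipsychotic daily dose, and anticonvulsant medications". The other is a linear mixed-effects comparison of symptom change, whose terms are not given. Neither replaces the t-test as the primary analysis.

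**The concern.** Two variables known before treatment starts are natural candidates for the primary model: the baseline value of the outcome and the factor on which randomisation was stratified. The planned test adjusts for neither.

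A change score fixes the coefficient on baseline at 1. If the true regression slope of follow-up on baseline is below 1, subtraction over-corrects, and chance baseline differences between arms add noise to the estimate. Balancing the arms within centre removes some between-arm variation, but a t-test that leaves centre out still counts that variation in its standard error.

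At stake is the width of the confidence interval on the main question. The total is fixed at 100, and every sham patient undergoes repeated anaesthesia, so free precision is worth having. The article hopes for a definitive answer on efficacy, and a tighter interval serves that aim whichever way the result falls.

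**Working it through.** **Inputs from the protocol article.** Standardised effect d = 0.6, read as the difference in change divided by the SD of change; 45 per group; alpha 0.05; 1:1 allocation; centre strata 60/20/20.

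**Assumed inputs.** The article gives no SAPS SD, baseline/post correlation or centre effect. I use correlation ρ from 0.3 to 0.7, follow-up/baseline SD ratio k of 1 or 1.3, and share c of change variance due to centre from 0 to 20%.

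**1. The plan's own figure.** Two-sided t-test, noncentrality 0.6 × √(45/2) = 2.85 on 88 degrees of freedom. Power is 79.5% at 44 per group, 80.4% at 45 and 84.4% at 50. The stated 45 reproduces exactly. Sidedness is not stated, but two-sided is the reading that gives 45. A 10% dropout allowance gives 45/0.9 = 50.

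**2. Adjusting for baseline.** With baseline SD s0 and follow-up SD s1:

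- Var(change) = s0² + s1² − 2ρ·s0·s1
- Residual variance after adjusting for baseline = s1²(1 − ρ²)
- Difference = (s0 − ρ·s1)², which is never negative

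Apart from one degree of freedom, adjustment therefore cannot do worse. With k = s1/s0, the variance ratio is k²(1 − ρ²)/(1 + k² − 2ρk), which reduces to (1 + ρ)/2 when k = 1. Power at 45 per group uses effective d = 0.6/√ratio on 87 degrees of freedom.

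| ρ | k | Variance ratio | Interval width vs t-test | Power at 45 per group |
|---|---|---|---|---|
| planned t-test | – | 1 | 1 | 80.4% |
| 0.3 | 1 | 0.65 | 0.81 | 93.7% |
| 0.5 | 1 | 0.75 | 0.87 | 90.1% |
| 0.7 | 1 | 0.85 | 0.92 | 86.3% |
| 0.3 | 1.3 | 1.538/1.91 = 0.81 | 0.90 | 88.0% |
| 0.5 | 1.3 | 1.268/1.39 = 0.91 | 0.95 | 83.8% |
| 0.7 | 1.3 | 0.862/0.87 = 0.99 | 1.00 | 80.7% |

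The gain vanishes where the slope ρk equals 1, for example at k = 1/0.7 = 1.43 when ρ = 0.7. With k = 1, the number per group for 80% power is 30, 34 and 39 at ρ = 0.3, 0.5 and 0.7, against 45.

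**3. Leaving centre out.** If the arms are balanced within centre and centre explains a share c of the variance of change, the t-test's standard error is too large by about 1/√(1 − c). The approximate type I error is 2 × [1 − Φ(1.96/√(1 − c))].

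| c | 1/√(1 − c) | Type I error, formula | SE ratio, simulated | Type I error, simulated |
|---|---|---|---|---|
| 0 | 1.00 | 5.0% | 1.00–1.02 | 4.3–5.3% |
| 5% | 1.03 | 4.4% | 1.00–1.02 | 4.6–4.8% |
| 10% | 1.05 | 3.9% | 1.05–1.08 | 3.0–3.9% |
| 20% | 1.12 | 2.8% | 1.11–1.12 | 2.7–3.1% |

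The simulations used 100 patients, strata 60/20/20, permuted blocks of 2, 4 or 6 (an assumed set) and 6,000 runs per scenario; the ranges cover ρ = 0.3, 0.5 and 0.7. With 6,000 runs, a true 5% carries a simulation standard error of √(0.05 × 0.95/6000) = 0.3 percentage points.

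At c = 0 the standard error was right although baseline was not a covariate. Omitting baseline costs precision but does not invalidate the test.

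**4. Both together.** At ρ = 0.5 and k = 1, adjusting for baseline and centre gives power at 45 per group of 91.5% (c = 5%) and 92.9% (c = 10%).

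**The case against.** The plan is coherent as it stands. It sizes and analyses the trial with the same test, the stated power is met, and under 1:1 randomisation the t-test is unbiased. Chance baseline imbalance is random error already reflected in its standard error. The size of the gain rests on quantities the article does not give. Larger spread after treatment is plausible if some patients respond strongly and others do not, and then the benefit can be close to nothing. All of this stands. It limits the point to efficiency and stops any single figure from being quoted as the gain.

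Three stronger readings are tempting, and the document does not support them:

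- **That baseline is ignored.** It is not, because a change score subtracts it. What is missing is adjustment with an estimated slope. Nor does a correlation below 1 by itself imply over-correction; the condition is that the slope ρ·s1/s0 is below 1.
- **That the error bars are wrong in general, or that false positives rise.** The standard error is off only through the omission of centre and only as far as centre predicts SAPS change. It then errs towards intervals that are too wide.
- **That the responder model leaves out baseline SAPS and centre.** Its covariate list is open ("adjusting for variables including age, sex, duration of illness, antipsychotic daily dose, and anticonvulsant medications"). The text shows only that the two are not named, and a fuller protocol or analysis plan may name them. The same holds for the unstated terms of the mixed model.

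What survives is the primary test itself, which the article fixes as an unadjusted t-test.

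**Conclusion.** The point holds as a recommendation on efficiency. It is not a claim of invalidity or underpowering.

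For equal SDs and ρ between 0.3 and 0.7, the unadjusted test forgoes a variance reduction of 35% to 15%. At an SD ratio of 1.3 the forgone reduction is about 19% to 1%. The direction does not depend on these assumptions, since adjusting for baseline cannot increase the residual variance beyond the loss of a degree of freedom.

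The centre effect is a secondary matter. It is negligible if centre explains 5% of the variance or less, and becomes a visibly conservative test at 10% to 20%. The article gives no evidence on which case applies.

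**What to change.** Before unblinding, prespecify the primary estimate as the adjusted ECT minus sham difference in SAPS after the 9th session (or in change, which gives the same treatment estimate once baseline is in the model). Use a linear model with arm, baseline SAPS and study centre, and report the 95% confidence interval. Keep the two-sample t-test as a supportive analysis.

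No new data or patients are needed, and 50 per group can stay. The Sample size text should add that the t-test calculation is retained as the basis for sizing and that the primary model is adjusted.

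The cost is three degrees of freedom (one for baseline, two for centre) and a protocol modification, which the article's Ethics section says goes to the registry, the ethics committee, the funder and the journal.
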